### Missing data

Multiple imputation by chained equations (MICE) will be applied under the missing-at-random assumption. Sensitivity analyses will verify robustness.

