#### Exclusion criteria 

Life expectancy < 6 months (e.g., advanced malignancy); Severe hearing or cognitive impairment precluding assessment.

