### Recruitment and data collection

This is a multicenter, bidirectional cohort study. Eligible participants will be consecutively enrolled from nephrology and internal medicine departments across seven hospitals in Beijing. Retrospective data extraction will be performed only at the coordinating center (Beijing Chaoyang Hospital), while all participating centers will contribute prospective data collection. Pre-admission and admission-related baseline data, including demographic, clinical, and laboratory characteristics, will be retrospectively extracted from the electronic medical records (EMRs) at the coordinating center for eligible historical cases, while baseline standardized assessments will be prospectively performed at hospital admission for newly enrolled participants across all participating centers starting on January 3, 2025. During the prospective data collection phase, each participant will undergo standardized assessments encompassing: structured questionnaires for demographics, comorbidities, physical examinations and anthropometric measurements; laboratory tests including blood and urine biochemistry, inflammatory and metabolic indicators; geriatric assessment scales, frailty, cognition, nutrition, psychological state, physical performance. Collected variables were categorized into two groups: routinely available clinical indices (demographics, medical history, anthropometric measures and laboratory tests) and non-clinical indices, defined as non-routinely acquired geriatric assessment data (frailty scales and cognitive, functional, nutritional, and psychological assessments), which require specialized evaluation and are resource-intensive in routine clinical practice. All data will be entered into a harmonized electronic case-report form (eCRF). The database will be centrally curated at Beijing Chaoyang Hospital, following prespecified data quality control and harmonization procedures described below.

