### Measurements

#### Primary outcome

Frailty status in elderly CKD patients is defined using the FRAIL scale (Fatigue, Resistance, Ambulation, Illness, and Weight Loss; total score ≥ 3 indicating frailty). The primary analytical objective is to examine associations between clinical and non-clinical indices and frailty status and to support the development of individualized frailty risk prediction models.

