#### Secondary outcomes

Secondary outcomes comprise multidomain geriatric indicators related to frailty and intervention guidance: Cognitive function: Mini-Mental State Examination (MMSE) or Montreal Cognitive Assessment (MoCA); Nutritional status: Mini Nutritional Assessment–Short Form (MNA-SF); Psychological status: anxiety and depression; Comprehensive Geriatric Assessment (CGA) including physical performance (gait speed, grip strength, chair-stand test), functional ability (ADL, IADL).

Variable definitions will follow KDIGO 2024 and AWGS 2019 guidelines to ensure inter-center comparability. The integrated dataset will be used to identify older CKD patients at high risk for frailty and to generate individualized decision-support recommendations for nutritional, psychological, and physical-activity interventions through interpretable AI models.

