### Knowledge-distillation-based model optimization

A teacher–student learning framework will be implemented. The teacher model is trained using full indices including both clinical and non-clinical indices. The student model, restricted to routinely available clinical indices only, is trained by minimizing the distillation loss between teacher and student outputs, enabling the student model to learn compressed representations capturing information patterns related to geriatric assessment and frailty evaluation from routinely available clinical data. This strategy allows simplified deployment of the prediction model in routine clinical environments with limited data availability.

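### Multiple imputation under MAR is stated without exception, so performance tests left blank because the patient could not do them would be imputed too favourably, weakening the performance–frailty association

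*Protocol article*

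**What the plan says.** - **Rule for missing values** (Missing data): "Multiple imputation by chained equations (MICE) will be applied under the missing-at-random assumption". The only addition is "Sensitivity analyses will verify robustness". No variable or reason for missingness is set apart, and no missing-not-at-random scenario is named.
- **Tests concerned** (Secondary outcomes): "physical performance (gait speed, grip strength, chair-stand test". ADL and IADL are collected alongside them.
- **Who is tested, and when**: the Exclusion criteria remove patients with "Severe hearing or cognitive impairment precluding assessment" or a short life expectancy. They do not remove those who cannot walk or rise from a chair. Under Recruitment and data collection, "baseline standardized assessments will be prospectively performed at hospital admission for newly enrolled participants".
- **Where the values go**: the Primary outcome section makes associations of clinical and non-clinical indices with frailty the main analytical objective. The knowledge-distillation section adds that "The teacher model is trained using full indices including both clinical and non-clinical indices". Outcomes and analysis lists causal learning about the contributors to frailty.
- **Primary outcome**: the FRAIL scale, "Fatigue, Resistance, Ambulation, Illness, and Weight Loss; total score ≥ 3 indicating frailty". The three performance tests are not part of it.

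**The concern.** MAR means that, given the observed data, the chance of a value being missing does not depend on the value itself. A chair-stand test left blank because the patient could not stand breaks this: the blank exists because performance was very poor. MICE fills it from the relation seen in patients who completed the test, so the weakest patients receive values typical of stronger ones.

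Inability is foreseeable in patients aged 60 or over with CKD who are assessed on admission. At stake is the estimated relation between physical performance and frailty, which belongs to the primary association objective and feeds the causal analysis and the teacher model. The promised sensitivity analyses cannot recover it unless the data show which blanks were due to inability.

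**Working it through.** **The plan's own figures.** The Missing data section gives none. The sample-size inputs used below reproduce: 10 × 30 / 0.20 = 1,500, and 1.96 × √(0.20 × 0.80 / 1,500) = 0.0202, matching the stated ±2%.

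**Inputs from the article.** N = 1,500; frailty prevalence 20%.

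**Inputs assumed, because the article gives none.**
- One standardised performance score, missing for the lowest 5%, 10% or 20% of true capacity.
- One covariate correlated r = 0.3 to 0.85 with the score, standing for whatever enters the imputation model.
- Frailty status in or out of that model.
- Correlation 0.7 between capacity and the latent frailty score.

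**Method.** Normal-model multiple imputation with proper draws, 5 imputations, 60 replicates, 24 scenarios.

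**Truth, in closed form.** With share unable p and cut-off c, the mean of the unable is -φ(c)/p and that of the tested is φ(c)/(1 - p). For p = 0.10, φ(c) = 0.1755, giving -1.75 SD and +0.20 SD. For frailty at 20%, φ = 0.280, so the frail versus non-frail difference is -0.7 × (0.280/0.20 + 0.280/0.80) = -1.23 SD. The simulation agrees.

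**Share of gap recovered** = (tested mean - imputed mean) / (tested mean - true mean of the unable). Example with r = 0.5 and frailty in the model: (0.20 + 0.53) / (0.20 + 1.75) = 0.37.

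Results at 10% unable:

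| r | Frailty in model | Imputed mean (SD) | Gap recovered | Frail - non-frail (SD) |
|---|---|---|---|---|
| 0.3 | no | +0.07 | 7% | -0.64 |
| 0.3 | yes | -0.35 | 28% | -0.88 |
| 0.5 | no | -0.17 | 19% | -0.72 |
| 0.5 | yes | -0.53 | 37% | -0.93 |
| 0.7 | no | -0.60 | 40% | -0.86 |
| 0.7 | yes | -0.83 | 52% | -1.00 |
| 0.85 | no | -1.06 | 65% | -1.00 |
| 0.85 | yes | -1.19 | 71% | -1.08 |

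At 5% unable, 7% to 73% of the gap is recovered and the difference is -0.85 to -1.14 SD. At 20% unable, 5% to 66% is recovered and the difference is -0.39 to -1.01 SD. In all 24 scenarios the imputed values are too good and the association is attenuated, by roughly (1.23 - 1.14)/1.23 = 7% up to (1.22 - 0.39)/1.22 = 68%.

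**Effect on discrimination.** This is a second assumed set-up: latent fitness drives gait (r = 0.8), two routine covariates (r = 0.5 and 0.4) and frailty (logit slope -1.3, prevalence 18%). With 10% unable, the AUC of gait alone falls from 0.738 to 0.705; coding inability as the worst observed value keeps 0.737. A teacher-like logistic model that also has ADL, IADL and grip strength (assumed r = 0.65 to 0.7, observed in the unable), with those variables informing the imputation, changes much less:

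| Unable | AUC, complete data | AUC after MAR imputation |
|---|---|---|
| 5% | 0.769 | 0.768 |
| 10% | 0.768 | 0.765 |
| 15% | 0.774 | 0.768 |

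**The case against.** The strongest reply is that the article never says inability is stored as a missing value. The quality-assurance section refers to assessment manuals, implementation checklists, a standard CRF and central missing-data procedures. Any of these may already score inability, in which case the imputation rule never reaches it. Coding detail of this kind often sits outside an article. This stands as a condition on the point: a reader might infer that the main analysis is wrong by rule, but the text supports this only for values actually left blank through inability. It does not remove the point, because the rule that is printed admits no exception.

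Three stronger readings are tempting and not supported.

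- **That the frailest patients would be given near-average performance.** MICE conditions on other variables. ADL, IADL and the FRAIL ambulation and resistance items are collected, though the article does not say what enters the imputation model. Near-average values arise only with weak predictors (5% to 7% of the gap recovered at r = 0.3 without frailty status). With frailty status and r = 0.5 to 0.85, 31% to 73% is recovered: still too good, but less so.
- **That frailty itself would be misclassified.** FRAIL ≥ 3 uses none of the three tests, so prevalence and outcome status are unaffected.
- **That the prediction models would be materially damaged.** The AUC loss from 0.738 to 0.705 is for one test alone, and no single-test model is planned. With related inputs present the loss is about 0.001 to 0.006. The article's non-clinical indices also include frailty scales, which leaves these tests less to add. The student takes no performance test as input.

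**Conclusion.** The point holds in a limited form. The stated rule, applied to performance tests blank through inability, biases those values toward better performance and attenuates the performance–frailty association. The direction is firm: it follows from the mechanism and appeared in every scenario. The size is not known. It rests on an assumed share unable (5% to 20%), assumed correlations and the simplification that the unable are exactly the lowest tail of capacity. On those inputs a true difference of about -1.23 SD becomes -0.39 to -1.14 SD. At 10% unable, with frailty status and a covariate of r = 0.5 to 0.85 in the imputation model, it becomes -0.93 to -1.08 SD.

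The effect falls on the association and causal results and on the description of the performance measures. Frailty classification and sample size are unaffected, and teacher and student discrimination probably change little. It is worth correcting because the unspecified sensitivity analyses cannot separate inability from other reasons unless the reason is recorded.

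**What to change.** Unless the assessment manual or eCRF already does this (in which case one sentence in the Missing data section saying so is enough):

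1. For each performance test, record *not done: physically unable* separately from *not done: other reason*.
2. In the association, causal and teacher analyses, enter inability as a lowest category, or as the worst value plus an indicator.
3. Restrict MICE to values missing for other reasons. For the association analyses, include ADL, IADL and the FRAIL items in the imputation model.
4. Name a missing-not-at-random sensitivity analysis, for example one that shifts imputed values downward where the reason remains unknown.

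**Cost.** One eCRF field and a few lines of analysis text. The Trial status section expects recruitment to run to December 31, 2027, so most of the information can still be captured prospectively. Patients enrolled since January 3, 2025 need a check of the notes, and some reasons will not be recoverable. The worst-category code is a convention and should be described as one.

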### Ethics and data security

De-identified data will be stored in secure servers with role-based access. Any protocol amendment will be reported to the central ethics committee and the trial registry.

## Discussion

Frailty in elderly CKD represents a dynamic, modifiable continuum rather than a fixed state [11–13, 34, 35]. Traditional assessments fail to capture individualized causal pathways linking renal dysfunction, inflammation, and functional decline [18–21]. By employing causal learning, this study aims to move beyond purely associative modeling toward improved mechanistic interpretability and clinically meaningful risk stratification [26–28], while knowledge distillation is expected to enhance scalability and applicability of the prediction framework in routine clinical settings with heterogeneous data availability [29–31].

This framework is designed to address real-world heterogeneity in frailty assessment availability across different healthcare settings. Comprehensive geriatric assessment is resource-intensive and not uniformly implemented across hospitals with different service capacities; consequently, many older patients with CKD lack complete geriatric assessment data and are often evaluated using routine clinical indicators only. To address this practical constraint, the proposed teacher–student framework is designed to extend frailty screening and intervention decision-support to data-limited clinical environments. The teacher model leverages comprehensive multimodal data when available, whereas the student model is optimized to operate using routinely collected laboratory and clinical variables. This design enables frailty screening and risk stratification under incomplete data conditions and supports broader applicability across healthcare settings with variable resource availability. In addition, the multicenter study design facilitates model development across heterogeneous CKD populations with different disease severity and comorbidity profiles, further supporting adaptability in diverse clinical environments.

The expected outcomes include the development of an interpretable AI-assisted frailty prediction framework, establishment of a multicenter CKD–frailty database, and provision of quantitative decision-support outputs to assist individualized risk stratification and care planning. In clinical practice, the proposed framework is intended to support frailty risk stratification and individualized care planning rather than replace clinical judgment. Model-generated frailty risk scores and interpretable feature contributions may assist clinicians in identifying high-risk patients who could benefit from comprehensive geriatric assessment and targeted interventions, while facilitating routine monitoring of lower-risk individuals in primary care settings. At the population level, standardized risk outputs derived from multicenter data may contribute to evidence generation for defining frailty risk thresholds and stratified management pathways, thereby providing supportive data for future clinical pathway optimization and guideline refinement.

Several limitations should also be acknowledged. First, model performance may be influenced by temporal changes in patient characteristics and treatment patterns, potentially leading to model drift. To minimize this impact, continuous data updating and periodic model recalibration will be implemented within the bidirectional cohort framework. Second, although knowledge-distillation techniques enable prediction using laboratory-only inputs, the inferred representations of clinician-rated frailty and geriatric assessment information derived from laboratory features require further validation. This limitation will be addressed through prospective data collection and external validation across broader and more diverse patient populations. Third, residual heterogeneity across participating centers may persist due to variations in clinical practice patterns and healthcare infrastructure. This will be mitigated through standardized assessment and implementation protocols, centralized quality control procedures, and harmonized data management strategies implemented across all study sites.

Ultimately, this project aims to integrate advanced computational modeling into everyday geriatric nephrology workflows, providing clinicians with supportive, patient-specific risk information while maintaining physician oversight and final clinical decision authority, thereby supporting safe and responsible integration into routine geriatric nephrology workflows.

### Trial status

Recruitment commenced on January 3, 2025, with completion anticipated by December 31, 2027. Final analyses are anticipated by mid-2028.

## Data Availability

Data will be available from the corresponding author upon reasonable request after study completion.

## Abbreviations

CKD: Chronic Kidney Disease
FRAIL: Fatigue, Resistance, Ambulation, Illness, Loss of Weight
MNA: SF—Mini Nutritional Assessment Short Form
MMSE: Mini Mental State Examination
MoCA: Montreal Cognitive Assessment
GDS: Geriatric Depression Scale
KDIGO: Kidney Disease: Improving Global Outcomes
AI: Artificial Intelligence
